## 5. Intervention

All community members with valid consent will be offered PZQ+ALB, delivered by community health nurses/trained field staff. This will involve community sensitisation within the selected villages, and then enrolment of participants with exclusion of school-enrolled children who received MDA, children less than one year of age, and (for ALB) women in their first trimester of pregnancy in accordance with current WHO recommendations. Participants in the community-based survey will be invited to join a whole community treatment MDA day, where they will receive a baseline and a 12-month treatment of 600 mg PZQ at 40 mg/kg body weight and a single dose of 400 mg ALB. The research team will conduct the parasitological examinations and questionnaires, and the whole community MDA will take place after all of the samples have been collected as arranged with the community leaders.

## 6. Individual Random Selection for Parasitological Examinations and Questionnaires

The study is an augmentation to the current standard of care (annual school-based MDA). With a longitudinal study design, random selection is only required at the individual level for parasitological and epidemiological investigations; all of the individuals in the community will be offered treatment. In each community, following sensitisation, households will be enumerated, with approximate number of residents recorded. Based on the number of households and indicative number of residents in each community, households will then be randomly selected according to a process of selecting every other (odd number houses) household to achieve the sample size. Where a household, or an individual within a household refuses, or is absent during the study, the household will be replaced by the next enumerated household. All the residents within the selected households will be requested to provide urine and stool specimens, and to complete questionnaires. At this stage, individual consent will be elicited, with age, sex, and school-attending status recorded and a unique participant identification number allocated. Selection will proceed until the minimum sample size is achieved. All community members will be invited to receive treatment, with additional consent elicitation by field staff. Treatments will be directly observed, and treatment coverage data will be recorded for all individuals.

For comparison to annual school-based MDA, a junior school (comprising children aged 6–14 years in classes 1 to junior high 3) will be selected at the time the national NTD Control Programme visit occurs. Prior to the deworming, school directors and class teachers will be asked to prepare class lists with the name, age, and sex of the children. Class lists will be imported into Microsoft Excel and each individual will be assigned a computer-generated random number. Individuals will then be selected by study investigators in ascending number order. Individuals who are not present on the day will be replaced by the next individual on the list, until the minimum sample size for parasitological testing is achieved.

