## 4. Study Design

This longitudinal study will comprise baseline and follow-up surveying of the same individuals. Baseline surveying will involve screening urine and stool samples from a random selection of participants to assess infection prevalence and intensity, and conducting questionnaires to determine associations with WASH and morbidity from both schistosomiasis and STH. Qualitative focus group discussions and in-depth interviews will be held with community members and key informants to assess the understanding of the current MDA strategy, its strengths, and weaknesses, and to identify the feasibility and acceptability of expanding treatment in communities. Comparisons will be made: (i) after 6, 12, and 18 months; and, (ii) to the provision of annual MDA in the regular National School-Based Deworming Programme in schools in the same health districts, at the same time points as a means of comparison to the existing school-based deworming programme in similar prevalence settings. Drug treatment coverage for each survey will also be measured.

This study will involve expanding access to PZQ+ALB treatment for the broader population, including preschool-aged children, out-of-school school-aged children, and adults, including pregnant women. An annual community-based PZQ+ALB treatment will be provided by community health nurses and trained field staff, with cross-checking of enrolled school-aged children so as not to double-up treatments that have been provided in school-based MDA. Treatment will be provided at baseline and 12 months, and the associated reductions in prevalence and intensity of schistosomiasis and STH will be assessed (Figure 2). Parasitological examinations and questionnaires will be conducted on a random sample of participants to determine associations with morbidity from both schistosomiasis and STH, and investigate the feasibility of scale-up. An experienced and trained social science team will conduct qualitative interviews with teachers that are involved in administering annual MDA, and focus group discussions with purposively selected groups of participants by gender, age, and socio-economic status, as well as parents and caregivers.

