## 15. Sample Size Calculation

Sample size calculations are for the primary outcome, assuming a baseline schistosomiasis prevalence of infection of 20%. Sample size calculations are calculated separately for baseline and follow-up. 

Baseline sample size: This was estimated using a hypergeometric formula (due to small overall community size):$$n=Nz^{2}\rho q/\left(E^{2}\left(N-1\right)+z^{2}\rho q\right)$$
where: *N* = population size (1500 people); *p* = estimated prevalence (0.2); *q* = 1 − *p*; *E* = accuracy of estimation (0.03); *z* = 1.96 (confidence level 95%).

A 40% buffer was applied to take into account differences in necessary covariates (including age and sex). The baseline sample size per site is 658 people per community of 1500 people. Assuming three communities, 1974 participants will need to be sampled for parasitology and questionnaires.

Follow-up sample size: It is assumed that there will be a post-intervention reduction in prevalence of 50% (i.e., from prevalence of 20% to 10%; see outcomes). This gives an assumed baseline population of 132 ‘infected’, and first-round follow-up of 66 ‘cured’. An additional 20% buffer for age and sex (10% each), and a 10% loss to follow-up between each follow-up have been added. Using a sample size formula for matched proportions:$$\;n={\left(Z_{\frac{\alpha }{2}}+Z_{\beta }\right)}^{2}\;\times \;\left[p_{0}\left(1-p_{0}\right)+p_{1}\left(1-p_{1}\right)\right]/{\left(p_{0}-p_{1}\right)}^{2}$$
where: *n* = number of individuals required; (*Z*_α/2_ + *Z*_β_)² = test statistic of 7.85, based on standard normal distribution values assuming significance of 0.05 and power of 80%; *p*_0_ = estimated prevalence at baseline (20%); *p*_1_ = estimated prevalence at follow-up (10%).

Assuming a 60% buffer, 314 participants per site will need to be longitudinally followed up each round. Therefore, for three study sites, a total of 942 subjects would be targeted to be followed up.

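### Section 6 replaces a whole household when one resident refuses or is absent, which drops willing members and tilts the sample towards households where everyone is present and consents

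*Protocol article*

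**What the plan says.** Section 6 states that "random selection is only required at the individual level for parasitological and epidemiological investigations", but the procedure it describes works on households. After enumeration, "households will then be randomly selected according to a process of selecting every other (odd number houses) household to achieve the sample size". Everyone in a chosen house is approached: "All the residents within the selected households will be requested to provide urine and stool specimens, and to complete questionnaires". The replacement rule treats one person's refusal or absence like that of the whole house: where "an individual within a household refuses, or is absent during the study, the household will be replaced by the next enumerated household". Recruitment is open-ended: "Selection will proceed until the minimum sample size is achieved".

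Other parts of the article handle participation person by person. Section 6 itself takes individual consent once a household has been selected. Section 11 (Eligibility Criteria and Justification) keeps a person without a signed form out of the parasitological analyses and says nothing about the rest of the house. Section 15.1 (Informed Consent) separates the consent forms so that a person may accept some procedures and decline others.

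On follow-up, Section 4 says: "This longitudinal study will comprise baseline and follow-up surveying of the same individuals".

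**The concern.** Three things look wrong.

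- **Willing people are discarded.** A household stays in only if every resident is present and agrees. The chance of that falls with household size, and the sample shifts towards fully present, fully consenting households. Section 1 attributes schistosomiasis to water contact, and Section 7 hands out specimen pots in the morning for return the same day. People away for water-related work are plausibly both more exposed and more often absent. Their housemates, who may share that exposure, would go with them. Baseline prevalence is the starting point of the primary outcome, and the multiple imputation or weighted GEE planned in Section 14 cannot readily repair this, because replaced households supply no survey data.
- **Field teams have conflicting instructions.** They cannot both drop a household for one refusal and treat consent as an individual matter.
- **The timing is open.** The rule covers absence at any point in the study. Applied at 6, 12 or 18 months, it would contradict following the same people.

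**Working it through.** **1. The target reproduces.** Section 15 gives N = 1500, p = 0.2, E = 0.03, z = 1.96. The formula N z² p q / (E²(N−1) + z² p q) gives 469.5, rounded up to 470. Then 470 × 1.4 = 658 per community, as stated. The 40% buffer is assigned to covariates such as age and sex, not to refusal or absence.

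**2. Share of households replaced.** Let a be the individual chance of refusal or absence and k the household size. With independence, the share replaced is 1 − (1−a)^k. Neither a nor k is in the document, so both are assumed.

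| Household size | a = 5% | a = 10% |
|---|---|---|
| 2 | 10% | 19% |
| 5 | 23% | 41% |
| 8 | 34% | 57% |

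**3. Effect of clustering.** Take household size as 1 + Poisson and a = 10%. With mean size 5, the share replaced is 40% under independence and 26% with an assumed within-household correlation of 0.3. With mean size 4, it is 33% and 23%.

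**4. Effect on household size.** With mean size μ, the mean size of kept households is 1 + (μ−1)(1−a). For μ = 5 and a = 10%, this is 1 + 4 × 0.9 = 4.6, a fall of 8%.

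**5. Supply from odd-numbered houses.** Half of 1500 is 750, and 658/750 = 87.7%. More than 12.3% ineligible, absent or refusing would exhaust the list even if only individuals were lost. Under the whole-household rule, the residents left are 750 × (1−a) × exp(−(μ−1)a) × [1 + (μ−1)(1−a)] / μ. For μ = 5 and a = 10%: 750 × 0.9 × 0.670 × 4.6 / 5 = 416.

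| a | Only the missing individuals lost | Whole household lost, mean size 4 | Whole household lost, mean size 5 |
|---|---|---|---|
| 2% | 735 | 682 | 668 |
| 5% | 712 | 590 | 560 |
| 10% | 675 | 463 | 416 |
| 20% | 600 | 280 | 226 |

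These counts precede the Section 11 exclusions (school-enrolled children, infants, the acutely unwell, the recently dewormed). With clustering of 0.3 at a = 10%, complete households in the whole community hold 1116 (mean size 4) or 1078 (mean size 5) people, so odd-numbered houses hold about 558 or 539, still below 658. In an odd-number scheme the following house on the list is an even-numbered one.

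**6. Willing people set aside.** At a = 10% with independence, the difference is 675 − 463 = 212 (mean size 4) or 675 − 416 = 259 (mean size 5) present, consenting residents of odd-numbered houses. That is 31% or 38% of the 675. The avoidable bias in prevalence is that share times the prevalence gap between willing people in kept and in replaced households. To equal the plan's own 3-point precision, the gap would have to be 0.03/0.314 = 9.6 or 0.03/0.384 = 7.8 percentage points. The document gives nothing from which to estimate the gap.

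**The case against.** The strongest reply is that the sentence is loose drafting. Sections 11 and 15.1 handle consent individually, and Section 12 speaks of enrolling all consenting selected households, so teams may in practice keep willing members. That may be so, but the rule names an individual's refusal or absence as a trigger for replacing the household. The conflict has to be settled in the text.

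Other replies stand and limit the point:

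- **Size.** The household-size shift is modest, absence probably clusters, and no bias in prevalence is demonstrated. The main contrast is within the same people, so selection threatens representativeness and the baseline level more than change over time.
- **Odd-numbered houses.** Taking alternate houses is ordinary systematic sampling, and no link between house position and infection is shown. The odd list is no hard cap either, because selection continues until the target is met. The 1,500 is a planning figure.

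A reader might also infer more than the article supports:

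- **That the cohort is broken.** At 10% loss in each of three rounds, 1 − (0.9³)⁵ = 79% of 5-person households would have at least one loss. That figure matters only if replacement runs at follow-up. The sentence sits in the enrolment sequence, Section 4 follows the same people, Section 15 allows 10% loss between follow-ups, and Section 14 plans for missing data. Only 314 of the 658 are needed at each round.
- **That treatment coverage is biased.** Section 6 invites all community members to treatment and records coverage for all individuals, whichever households are sampled.
- **That replaced households leave no trace.** Households are enumerated with approximate resident numbers before selection, so replacements can be identified.

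**Conclusion.** The point holds as a defect in the sampling rule. As written, one missing resident removes willing members, and retention falls with household size. At assumed independent rates of 5% to 10%, 23% to 41% of 5-person households would be replaced, and fewer if absence clusters. Selection on complete presence and consent matters more than the small change in mean household size. Baseline prevalence may be biased and the sample less representative; the size of any bias is unknown.

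The contradiction with individual-level consent is textual and needs no assumption. The 87.7% requirement follows from the plan's own figures. That even-numbered houses will be used, contrary to the stated scheme, is probable rather than certain: before eligibility exclusions, the odd list would suffice at 2% absence but not at 5% under the household sizes assumed. Replacement at follow-up is an ambiguity to close, not a demonstrated break in the cohort.

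**What to change.** Rewrite the selection paragraph of Section 6 so that:

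1. The enumerated households are put in computer-generated random order, as the same section already does for school children, and teams work down that order until 658 people are enrolled. Replacements then come from a defined place in the list.
2. Every consenting eligible member of a selected household is kept when others refuse or are absent.
3. A household is replaced only if it refuses or is absent as a whole, and only at baseline.
4. There is no replacement at 6, 12 or 18 months.
5. Household and individual non-response are reported.

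The cost is new wording, a column of random numbers, incomplete households in the data and slightly more record keeping. The sample size does not change. The change has to come before households are selected, because baseline specimens not taken from willing people cannot be recovered later.

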## 7. Sample Collections and Questionnaires

Since urogenital and intestinal schistosomiasis, and STH are co-endemic in most endemic communities, selected study participants will be requested to provide both faecal and urine samples. Participants will be given collection pots for urine and stool samples first thing in the morning and asked to return the pots the same day; all the diagnostics will be performed on the same day in order to maintain sample quality. Stool samples will be further stored on ice packs and subsequently in the freezer for any molecular analyses for quality control. Questionnaires will be conducted with these participants at baseline and follow-up by trained field staff; the questionnaires take approximately 30 min to complete, and there are 45 questions in the household questionnaire and 63 questions in the individual questionnaire. Socio-economic and WASH information, previous treatment received, and general morbidity information will be collected through self-reported questionnaire responses within these questionnaires. These data will be used to assess risk factors that are associated with prevalence and/or intensity of schistosomiasis and STH infection, and separately, associations between intensity of infection and morbidity indicators.

## 8. Parasitological Diagnoses

Faecal samples will be examined using the Kato-Katz kit from Sterlitech and compound microscopes (Olympus model CH and Boshida BD-SW30) at ×400 magnification. This will allow for the detection of *S. mansoni* and STH eggs and for the intensity of infection to be calculated as eggs per gram (epg). Urine samples will be visually examined for blood presence (macrohaematuria), tested with Urit 10 V reagent strips for microhaematuria, and filtered to examine the presence and intensity of *S. haematobium* infection. The filtration will involve passing 20 mL of urine through a 25 μm pore Plastok nylon filter housed in a Swinnex filter holder from Fisher Scientific. POC-CCA assays (ICT International) may be used for the detection of *S. mansoni* antigens, and will be conducted according to the manufacturer’s instructions. Samples may additionally undergo qPCR testing at CSIR-WRI or LSTM, using multiplex Taqman DNA assays with species-specific probes (and viral-DNA control) [34]. Quality control checks will be carried out where 10% of the slides will be re-examined by a lead technician to ensure to confirm their positive or negative status. Any discrepancy between the two slide reads will require a re-examination of all the slides up to that point.

## 9. Qualitative Research

Qualitative data will be collected through semi-structured interviews (with those who distribute drugs, including, as appropriate, health workers in the community and school teachers within the schools), and focus group discussions with a purposively sampled range of community members receiving the additional drugs. Semi-structured interviews are conducted with individuals and are structured around key areas of enquiry [35], whereas focus group discussions are held with groups of people with similar characteristics [36]. Community members will include a sample of men, women (including pregnant women) and children who have received the treatment. All qualitative data will be collected by trained and experienced social scientists. The quality of this qualitative data will be assured through training, debriefing, developing rapport with participants, and ensuring the use of open-ended and probing questions [35,37].

Additionally, because deworming treatments are not currently provided to the expanded community groups, qualitative mapping will be conducted to investigate the community structures through which expanded treatments could be provided in the future. Such sites could, for example, include health centres, aid posts, or outreach clinics, and treatments could potentially be included in existing health packages such as antenatal care, child immunisations, vitamin A distributions, maternal health checks, or health education services [13]. Qualitative exploration of community structure to support expanded treatments within the different communities and collaborative design of potential health system interventions, will be conducted following baseline surveying.

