## 2. Design/Methods

A multi-site longitudinal study will be conducted in Ghana to investigate the effectiveness of expanding treatment strategies for PZQ and ALB to community members in a peri-urban setting, where the risk of schistosomiasis and STH is considerable. The intervention will be assessed at 6, 12, and 18 months. Nested within this study will be qualitative and socio-economic evaluations that will explore the accessibility, feasibility, and economic impact of expanded treatment from different complementary perspectives. 

The specific objectives are:To conduct targeted baseline parasitological and epidemiological surveys to describe infection levels of schistosomiasis and STH, and associated WASH and morbidity indicators;To assess expanded annual community treatment in reducing prevalence of schistosomiasis and STH;To assess community understanding of the current MDA programme and its strengths and weaknesses and economic aspects of whole community treatment;To assess the acceptability and feasibility of introducing an alternative treatment strategy to the current treatment regimen from different perspectives;To investigate different levels of access and factors influencing scale-up of PZQ and ALB treatment in areas with limited treatment coverage.

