## 12. Sensitisation and Recruitment

Key programme and academic personnel have been involved in the study and its design since inception. These staff will coordinate the selection of sites and subsequently contact key local persons, including district health and education personnel, school and community leaders. A team leader will be assigned to each field team. Following site selection, team leaders will have primary responsibility for correct sensitization of communities, in accordance with established protocols and etiquettes (for example, contact via chiefs prior to community consultation). Recruitment of participants will be via community consultation, with enrolment of all consenting randomly selected households. Recruitment of school children for parasitological comparison will be via teachers, with take-home consent forms and accompanying information sheets being issued for parental consent. Children randomly selected for parasitological surveillance and questionnaires will be given sample pots for stool and urine samples and asked to bring them back the following day. To recruit participants for the focus group discussions and semi-structured interviews, a sampling frame of all of the eligible participants will be obtained. In line with the theory and practice of qualitative research, a purposive sample will then be taken within this study aiming to ensure maximum variation in age, gender, and socio-economic status, pregnancy, and involvement or otherwise in previous school-based distribution. Qualitative data will be collected until reaching the saturation point (when the research team are confident they have received the full range of experiences and responses) [40].

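### Section 9 restricts community focus groups to people who took the drugs, Sections 4 and 12 describe a wider sample, and none of them samples by uptake of the study MDA

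*Protocol article*

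**What the plan says.** Section 9 sets the community sample twice, each time by receipt of treatment. Focus groups are described as "focus group discussions with a purposively sampled range of community members receiving the additional drugs", and the next description reads "Community members will include a sample of men, women (including pregnant women) and children who have received the treatment". The semi-structured interviews in the same section are with distributors: "with those who distribute drugs, including, as appropriate, health workers in the community and school teachers within the schools".

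Two other sections describe the sample differently. Section 4 (Study Design) says of the baseline work: "Qualitative focus group discussions and in-depth interviews will be held with community members and key informants". One of its purposes is "to identify the feasibility and acceptability of expanding treatment in communities". Section 4 later describes "focus group discussions with purposively selected groups of participants by gender, age, and socio-economic status, as well as parents and caregivers". Section 12 (Sensitisation and Recruitment) says that for focus groups and interviews "a sampling frame of all of the eligible participants will be obtained", followed by a purposive maximum-variation sample over age, gender, socio-economic status, pregnancy and whether the person took part in earlier school-based distribution.

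This work serves the Section 2 objectives on acceptability and feasibility seen from several perspectives and on access: "To investigate different levels of access and factors influencing scale-up of PZQ and ALB treatment in areas with limited treatment coverage". It also serves secondary outcome (vi) in Section 13, which assesses access and critical success factors qualitatively.

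**The concern.** To have received the drugs, a person must have heard of the MDA day, been present, been eligible and agreed. A sample defined by receipt is therefore selected on what the access and acceptability objectives set out to study. First-hand reasons for declining, being away or not being reached are held by people outside that sample.

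If the Section 9 rule governs the groups held after treatment, the barriers to uptake would be under-reported, and adding more groups of the same kind would not bring them out. Section 16 intends the results to inform national and WHO policy on expanded treatment, so an account drawn from acceptors alone would matter.

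**Working it through.** No arithmetic applies. Qualitative sampling runs to saturation, no qualitative sample size is stated, and no figure in the article bears on who is interviewed. The check sets side by side every place that defines or could widen the sample.

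1. **Who is sampled.**

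| Place | Population | Treatment condition | Uptake of study MDA as a criterion |
|---|---|---|---|
| Section 9, focus groups | Community members | Yes, recipients | No, all are recipients |
| Section 9, interviews | Distributors (health workers, teachers) | Not applicable | Not applicable |
| Section 4, baseline | Community members, key informants | None | No |
| Section 4, focus groups | Participants by gender, age, socio-economic status; parents and caregivers | None | No |
| Section 12 | All eligible participants | None | No |

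Sections 4, 9 and 12 describe three different populations for the community focus groups. The nearest criterion in Section 12 is involvement in earlier school-based distribution. That concerns the existing programme, not the MDA under study.

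2. **Timing.** Section 5 places the community MDA after all samples have been collected. If the Section 4 baseline groups are held during baseline surveying, and so before the MDA, no member can yet have received the expanded treatment. They cannot meet the Section 9 description. They can give views on a proposal, but not reasons for missing or declining an MDA day that lies ahead.

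3. **Whether untreated informants can exist among participants.** They can. Section 15.1 takes separate consent for specimens, questionnaires and treatment, expecting that some people will agree to part only. A person can be enrolled and decline the drugs.

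4. **Whether another provision reaches them.**
   - Section 6 replaces households that refuse or are absent and describes no qualitative follow-up of them.
   - Deviant case analysis and triangulation (Section 15.2) work on data already collected and add nobody to the sample.
   - Saturation (Section 12) is judged within whichever group is sampled.
   - Distributors can report why people did not come forward, but second-hand.

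5. **Whether non-recipients can be identified.** Section 6 has treatment directly observed and coverage recorded for all individuals, and Section 15.2 keeps a participant register at each community site. Enrolled participants with no observed treatment can be listed from these. The household enumeration cannot serve for the whole community, because it records only approximate numbers of residents. Individual identifiers are given at enrolment in the selected households.

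**The case against.** The strongest reply is that the document as a whole is wider than Section 9. Section 4 explores acceptability at baseline, when nobody can have been selected on uptake. The Section 12 frame could include people who enrolled but declined treatment. Distributors see non-uptake directly. The verb in Section 9 says whom the sample includes, not that others are barred. The level of uptake does not depend on focus groups either, since coverage is a separate secondary outcome. Finally, a journal article may leave the detailed composition of groups to a fuller protocol.

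Much of this stands. A reader might infer from Section 9 that the entire qualitative sample is confined to people who took the drugs. Sections 4 and 12 and the distributor interviews do not support that. A reader might also infer that the study will overstate the level of access. The documents do not support that either, because coverage is measured separately from the qualitative work. Nor can the number of people left out be estimated from the coverage figures in Section 1. Those are for school-aged and preschool-aged children in existing programmes, while a study community also contains people not due community treatment.

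What the reply does not remove is narrower. Section 9 states the recipient condition twice, so it is stated text and not an omission through condensation. The Section 12 frame permits non-recipients but does not call for them. The baseline groups come too early to explain non-uptake.

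**Conclusion.** The point holds in a limited form. Section 9 is narrower than Sections 4 and 12, the three must be reconciled, and no section names people who refused, were absent or were not reached as a group to sample. If Section 9 is followed for the groups held after the MDA, community views on acceptability, access and scale-up will come from acceptors alone. Pre-treatment exploration of acceptability is not affected.

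The size cannot be stated: it depends on how many residents go untreated and how far their reasons differ from what distributors report, and the article gives neither. The conclusion rests on two assumptions: that the baseline groups precede the MDA, and that Section 9, as the dedicated methods section, would guide field teams where the sections differ. The change is worth making before the post-MDA groups are convened. It does not touch the primary outcome.

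**What to change.** 1. In Section 9, replace both recipient phrases with *eligible residents, whether or not they received the treatment*.
2. In Section 12, add uptake of the study MDA (took it; refused; absent or not reached) to the maximum-variation list.
3. State that non-recipients will be identified from enrolled participants on the register with no directly observed treatment recorded, subject to their consent to the qualitative work.
4. In Section 4, state that the baseline groups are held before treatment with community members in general.

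The cost is protocol wording and the reassignment of some planned groups or interviews. Non-recipients are harder to recruit, some may withhold consent, and some groups of treated people are given up. Step 3 still misses residents of households that were never enrolled, and the report should say so.
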